## Abstract

**Objectives:** Neglected tropical diseases (NTDs), such as leprosy, significantly impact mental health and overall well-being. This study aims to evaluate the effectiveness and acceptability of a mental health intervention targeting individuals affected by leprosy in Ethiopia. The intervention utilizes the Traumatic Stress Relief (TSR) program to target symptoms of posttraumatic stress disorder (PTSD), anxiety, and depression, and to improve overall mental health.

**Methods:** This exploratory randomized controlled trial (RCT) will recruit participants with lived experiences of leprosy. Participants will receive four group sessions of a low-intensity TSR intervention. The intervention will be administered by a pair of trained facilitators, including one mental health practitioner and one community member with lived experience of leprosy. Data will be collected through self-report questionnaires to assess changes in PTSD symptoms, anxiety, and depression. In addition, interviews will provide further insights into participants' experiences and the acceptability of the intervention.

**Discussion:** This exploratory trial will provide insights into the feasibility of mental health interventions for individuals affected by leprosy. The findings will inform the design of future trials to evaluate the effectiveness of such programs on a larger scale and in more diverse contexts.

**Trial Registration:** The UK's Clinical Study Registry: ISRCTN868254411

**Summary**

• The Traumatic Stress Relief (TSR) program addresses a critical gap in mental health support for individuals affected by leprosy, a population often marginalized and overlooked in healthcare systems.• By implementing a peer-supported group therapy model in Addis Ababa, Ethiopia, this research provides a scalable framework for improving psychological well-being among leprosy patients.• The program not only targets symptoms of posttraumatic stress disorder (PTSD), anxiety, and depression but also aims to reduce stigma and enhance social support networks within the community.• The impact of this research extends beyond immediate health benefits; it has the potential to inform public health policies and practices at local, national, and international levels.• By demonstrating the effectiveness of community-based mental health interventions, the TSR program can influence policymakers to adopt similar approaches for other neglected diseases and vulnerable populations.• Finally, the findings of this study may inspire further peer-supported strategies, fostering a more integrated approach to healthcare that recognizes the importance of mental health alongside physical health.

## 1. Introduction

Neglected tropical diseases (NTDs) are widespread in many developing tropical countries, leading to significant illness and impeding economic development in communities [1]. The research indicates that individuals with NTDs often experience a reduced quality of life due to their symptoms, emotional distress, and treatment challenges [2]. Specifically, those with visible deformities from conditions such as leprosy face significant difficulties [3].

Leprosy is a condition that primarily affects the skin and peripheral nerves. Leprosy remains a significant public health concern in many parts of the world with more than 200,000 new cases reported annually [4, 5]. Although leprosy is treatable and early intervention can prevent disability, the visible impairments and the stigma associated with the disease lead to challenges such as social exclusion [6], income loss and unemployment, and problems in access to public services in health and education [7], which all have been associated with poor well-being [8, 9]. In their study on mental health difficulties with leprosy patients, Soni, Kaur, and Kaur [10] reported that 14% of the participants had moderate to severe depression and almost one in five patients who showed symptoms of depression had attempted suicide. In another study, the overall prevalence of mental health difficulties such as depression and anxiety was found to be 34.6% among persons affected by leprosy [11]. Further studies from other leprosy endemic countries also reported a high prevalence of mental health difficulties [12–14].

However, the research on leprosy has primarily focused on its physical aspects, despite recent studies highlighting the need for mental health interventions to address the trauma caused by the disease [8]. Recent studies emphasize that while existing evidence supports increased investment in mental health interventions for individuals affected by NTDs, including leprosy, there remains a significant need for research [4, 15]. Thus, recent attention has begun to focus on health-seeking behaviors and recovery, although psychosocial interventions targeting leprosy-related well-being remain scarce due to limited resources in endemic countries, with a few exceptions [15, 16].

Further to that, low-resource settings, including many low- and middle-income countries (LMICs) and disaster-stricken regions, face severe shortages of mental health professionals [17]. For example, there are only 2.8 mental health workers per 100,000 people in South-East Asia and 1.6 in Africa, compared to 44.8 in Europe [18]. In Sierra Leone, for instance, there were just two psychiatrists for six million people following the Ebola outbreak, and in Ethiopia, there is about one psychiatrist per two million people and only an estimated 0.68 mental health professionals per 100,000 people.

In response, the World Health Organization (WHO) advocates for the use of scalable psychological interventions. These interventions are brief, manualized, and relatively easy to follow, making them suitable for implementation by trained and supervised nonspecialist staff. Designed to be scalable and adaptable, such interventions utilize new technologies or group formats to enhance accessibility. They can be deployed in various settings, including refugee camps, disaster zones, hospitals, and schools, effectively addressing common mental health disorders and often at no cost.

One example of scalable intervention, TSR, is the flagship program of Global Initiative for Stress and Trauma Treatment (GIST-T) developed by an international team of 25 experts from 13 countries. The program has been designed to train frontline professionals and nonspecialist staff to provide relief, especially in LMICs, by providing a structured, evidence-based approach to reduce symptoms of mental health difficulties [19].

The current project will test TSR's potential effectiveness in reducing symptoms of PTSD, anxiety, and depression. Specifically, it will evaluate the feasibility of recruiting individuals with leprosy for the TSR intervention, assessing its acceptability through various parameters such as recruitment rates, participant engagement, session attendance, and dropout rates. Qualitative interviews will further explore these aspects. The study will also define appropriate primary and secondary outcomes for assessing the intervention's effect in a full-scale trial. Data from this study will inform the design of a future multisite definitive clinical trial, including optimizing the design and planning the sample size. By focusing on this underserved population, the study aims to fill a critical gap in the literature and provide a foundation for future research on the effectiveness of mental health interventions for individuals with leprosy. The findings will have significant implications for public health strategies in similar contexts and could lead to the development of more comprehensive care models that address both the physical and psychological needs of individuals affected by leprosy.

## 2. Methods

The SPIRIT 2013 Statement: Defining standard protocol items for clinical trials was used in reporting this protocol. The trials received ethical approval from the City Government of Addis Ababa Health Bureau.

### 2.1. Study Design

This randomized controlled trial (RCT) with a qualitative component is designed to assess the effectiveness of the TSR intervention for individuals affected by leprosy in Addis Ababa, Ethiopia.

Methodological features of this feasibility RCT will minimize the possible bias in the intervention group. These features include allocation concealment (that will be ensured by randomization to be performed by an independent, off-site statistician), blinding (study statistician and the research team carrying out follow-up assessments will be masked to treatment allocation), use of intention-to-treat analysis, and the use of primary versus secondary endpoints.

The study will involve two arms: an intervention group receiving the TSR intervention and a waitlist control group. Participants will undergo individual randomization conducted by an off-site statistician. A total of 100 participants will be randomized in a 1:1 ratio into either the TSR intervention group (*n* = 50) or the waitlist control group (*n* = 50). Randomization will occur after baseline assessments using a computer-generated sequence to ensure allocation concealment.

As this study first of its kind and aims to demonstrate a trend in favor of the intervention and the recruitment and retention of participants into the study, the sample size was informed by community consultation and trial guidelines [20–25] to ensure a sample that allows for the estimation of recruitment and retention parameters, as well as potential effectiveness.

Participants will be included in the study if they meet the following criteria: (a) aged over 18 years, (b) able to give written informed consent—individuals with physical disabilities that may limit their ability to provide written consent will be permitted to give verbal consent, (c) leprosy-affected persons residing in the research sites, (d) score positive for depression on the Patient Health Questionnaire (PHQ-9), and (e) registered with a local health service. Although, to the best of our knowledge, there is no systematic mental health support specifically designed for individuals affected by leprosy, the limited available care may include counseling, therapeutic interventions, and pharmacological treatment, based on the severity of the condition. Such services are predominantly accessible within hospitals. However, these resources are frequently inadequate in rural regions, where both clinical expertise and diagnostic capabilities are often lacking. Consequently, individuals currently receiving any form of mental health support, such as individual or group psychotherapy, will be excluded from the study, as such interventions may confound the outcomes. Furthermore, individuals presenting with dissociation, psychosis, suicidal ideation, or substance use disorders will be deemed ineligible for participation. All participants will receive compensation for their time and contribution on a per-session basis.

Participants will be recruited from community settings where persons affected by leprosy reside, in partnership with organizations of persons affected by leprosy, with whom The Leprosy Mission Ethiopia have a long-standing working relationship such as ALERT Hospital and Ethiopian National Association of Persons Affected by Leprosy (ENAPAL).

Participants will also be recruited via referrals, and announcements will be shared with relevant organizations. Stakeholder engagement exercises will be conducted. Snowball sampling will be employed to initiate contact and encourage trial participation.

Eligible participants expressing interest in further information will be contacted by a member of the research team and provided with information about the study. This will include the aims of the study and a participant information sheet.

Participants will have up to 48 h to consider their participation in the study. Upon expressing interest, they will be provided with sufficient time to review and complete a consent form, followed by the assessment tools. The assessments will be administered by trained members of the research team at the participant's preferred location and conducted in their preferred language. While most assessments are self-report measures, the research team will be available to provide assistance to participants who prefer an interview-style format. This is particularly important for questions that may be complex to interpret or could elicit emotional responses. In addition, the research team will have access to support from mental health professionals at ALERT Hospital and the ENAPAL, if needed, during the screening process.

### 2.2. Intervention

Once consent is received, participants will attend four group sessions, delivered over a period of approximately three weeks. These sessions will be conducted in person at a designated location in Addis Ababa, with each group consisting of six to eight participants. Each session will last approximately 60–90 min and will focus on addressing the psychological and social impacts of leprosy. The sessions are designed to reduce symptoms of PTSD, anxiety, and depression. Please see Table 1 for further details.

The sessions will be facilitated by a pair of one mental health professional and one peer with lived experience of leprosy. While the primary facilitator delivers the session content, the peer facilitator will provide support based on their lived experience, creating a relatable and supportive environment. All sessions will also be monitored by a senior local therapist to ensure the highest standards of care and to provide immediate additional support if needed. Furthermore, all facilitators will follow a detailed protocol and a fidelity checklist and will receive ongoing supervision from experienced trainers to ensure that the intervention is delivered consistently and effectively. These trainers have over 25 years of experience in delivering protocols for individuals with mental health difficulties and psychosocial distress, as well as in training interventions in LMICs, with 8 years specifically focused on TSR.

The TSR training has many strategies [26, 27] to improve the accessibility and acceptability which is critical as persons affected by leprosy show low use of mental health services [28, 29]. For example, it does not require participants to share traumatic experiences with others and uses activities to reduce stigma [30, 31]. It can also be framed as both a training and a mental health intervention and delivered by local providers to beneficiaries. As a result, TSR content and teaching techniques have already been found feasible in Uganda, Rwanda, and Democratic Republic of Congo [19].

Furthermore, the intervention manual and all related materials have been reviewed by a group of representatives from the ENAPAL, The Leprosy Mission International Ethiopia, and mental health professionals to ensure cultural sensitivity.

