### 2.4. Data and Management

Summary statistics, means, medians, counts, and percentages along with corresponding measures of variability will be reported, along with 95% confidence intervals. The information gathered on the variability of the outcome measures will be sufficient to allow a formal sample size calculation to be made for the subsequent definitive RCT. The proportion of participants recruited and retained in the study will be reported along with 95% confidence intervals. A sample size of 100 will allow the recruitment/retention rates to be estimated with an accuracy of ± 8%.

One-way repeated measures analysis of variance to elucidate the impact of interventions on scores on all outcome tools while accounting for baseline characteristics of participants such as age, gender, and baseline severity of psychological symptoms will be employed. Mean and SD and effect sizes calculated as Cohen's d noted in this trial will inform sample size calculation for future definitive trials. The project will also have a clear Stop-Go criterion:• If the retention rate is 70% or higher, we will proceed with the full RCT as it is feasible.• If the retention rate is between 50% and 70%, we will explore methods to increase the retention rate to the required 70%. Alternatively, we may increase the required sample size to account for the higher drop-out rate.• However, if the recruitment rate is less than 50%, a full trial may not be feasible. In such cases, alternative approaches will be considered.

Subgroup analysis will be carried out with respect to age, duration of illness, number of previous episodes, and gender by adding a treatment with covariate interaction into the primary analysis model.

Data will be initially stored in a secured office location and subsequently digitized for storage on a secure network. In addition, all project-generated data will be assigned unique codes to protect participant confidentiality. Data associated with these codes and any identifiable information will be stored separately.

Descriptive statistics will be conducted for baseline and postintervention measures, including mean scores, standard deviations, and ranges. In addition, recruitment, attendance, and dropout rates will be reported to assess feasibility and acceptability.

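### The named analysis has no term for the TSR therapy groups: with a positive within-group correlation the standard error is modestly too small, and SDs alone are not enough to size the definitive trial

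*Protocol article*

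**What the plan says.** Section 2.1 (Study Design) sets the unit of randomisation: "Participants will undergo individual randomization conducted by an off-site statistician". It gives the size, "A total of 100 participants will be randomized in a 1:1 ratio", that is 50 per arm, and the arms, "an intervention group receiving the TSR intervention and a waitlist control group".

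Section 2.2 (Intervention) describes TSR as four in-person group sessions, "with each group consisting of six to eight participants". On staffing it says: "The sessions will be facilitated by a pair of one mental health professional and one peer with lived experience of leprosy". The number of facilitator pairs is not given.

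Section 2.4 (Data and Management) names the analysis, "One-way repeated measures analysis of variance to elucidate the impact of interventions on scores on all outcome tools", and its adjustment, "while accounting for baseline characteristics of participants such as age, gender, and baseline severity of psychological symptoms". All the covariates listed belong to the person. Neither therapy group nor facilitator pair appears, and the article nowhere mentions clustering or an ICC.

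The same section makes an unqualified claim about the next trial: "The information gathered on the variability of the outcome measures will be sufficient to allow a formal sample size calculation". The quantities it lists for that purpose are means, SDs and Cohen's d.

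**The concern.** At the postintervention comparison this is an individually randomised group-treatment trial, partially nested: TSR participants share a group, a facilitator pair and a peer, and waitlist participants as described do not. Group support is part of how the intervention is meant to work, and social support is among the primary outcomes in Section 2.3.1, so a positive correlation between members of one group is plausible. Repeated measures ANOVA allows for correlation between visits of one person. It does not allow for correlation between people in one group.

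Two things are at stake. Confidence intervals and p-values for TSR versus waitlist would be somewhat too favourable. The planning information for the definitive trial would also lack the quantity needed for a design effect, although supplying that information is a stated purpose of this study (Introduction) and the ability to calculate a sample size is one of its feasibility indicators (Section 2.3.1.8).

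**Working it through.** **Plan figure.** The article gives no ICC, power or standard error for the outcome contrast, so there is nothing to reproduce here. The ± 8% in Section 2.4 concerns recruitment and retention rates and does not bear on this point.

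**Inputs from the article.** 50 per arm, individual randomisation, groups of 6 to 8, waitlist comparator. **Assumptions.** ICC 0.01 to 0.10; two-sided 5% test; no grouping of controls at the postintervention assessment; all 50 TSR participants analysed.

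**Number of groups.** Six groups hold at most 6 × 8 = 48 people, and nine need at least 9 × 6 = 54. So 50 people form 7 groups (average 50/7 = 7.14) or 8 groups (average 50/8 = 6.25).

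**Formulas**, with m the group size:
- Design effect in the TSR arm: DE = 1 + (m − 1) × ICC
- Effective TSR sample: 50/DE
- Ratio of correct to naive SE of the difference: √((1 + DE)/2)
- True error of a nominal 5% test: 2 × (1 − Φ(1.96 / SE ratio))

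**Example, m = 7, ICC 0.05.** DE = 1 + 6 × 0.05 = 1.30. SE ratio = √(2.30/2) = √1.15 = 1.072. True error = 2 × (1 − Φ(1.96/1.072)) = 6.8%.

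| m | ICC | DE | Effective TSR n | SE ratio | True error, formula | True error, simulated |
|---|---|---|---|---|---|---|
| 6 | 0.01 | 1.05 | 47.6 | 1.012 | 5.29% | 5.3% |
| 6 | 0.05 | 1.25 | 40.0 | 1.061 | 6.46% | 6.5% |
| 6 | 0.10 | 1.50 | 33.3 | 1.118 | 7.96% | 8.2% |
| 7 | 0.01 | 1.06 | 47.2 | 1.015 | 5.35% | 5.2% |
| 7 | 0.05 | 1.30 | 38.5 | 1.072 | 6.76% | 6.9% |
| 7 | 0.10 | 1.60 | 31.2 | 1.140 | 8.56% | 8.5% |
| 8 | 0.01 | 1.07 | 46.7 | 1.017 | 5.40% | 5.2% |
| 8 | 0.05 | 1.35 | 37.0 | 1.084 | 7.06% | 7.0% |
| 8 | 0.10 | 1.70 | 29.4 | 1.162 | 9.16% | 8.5% |

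The simulation used 40,000 trials per row, 50 versus 50, no true effect, and a t-test ignoring groups. The m = 8 formula rows are an upper bound, because 50 people cannot all sit in groups of eight. The simulated layout there was four groups of 8 and three of 6.

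**Does the raw SD leave out the group variance?** The expected raw variance in the TSR arm, as a share of total variance, is 1 − ICC × (m − 1)/49. This is 1 − 0.05/49 = 99.9% at m = 6, ICC 0.01, and 1 − 0.70/49 = 98.6% at m = 8, ICC 0.10. The SD therefore contains almost all of it. What it cannot show is how the total divides between and within groups.

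**Consequence for the definitive trial.** With clustering in one arm, total n is multiplied by (1 + DE)/2. At m = 7 this is 1.15 for ICC 0.05 and 1.30 for ICC 0.10. As an illustration, assume d = 0.4, two-sided 5% and 80% power: 198 in total under independence, 198 × 1.15 = 227.7, so 228, at ICC 0.05, and 198 × 1.30 = 257.4, so 258, at ICC 0.10.

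**How well can this trial estimate the ICC?** With 7 groups of 7 and a true ICC of 0.05, the between/within variance ratio follows (1.30/0.95) × F(6, 42), and the ICC estimate is (F − 1)/(F + 6). The central 95% of estimates runs from about −0.12 to 0.28.

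**The case against.** The case on the other side has six parts.

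- **The harm depends on an unstated ICC.** This stands. At m = 7 and ICC 0.02 the SE ratio is only 1.03 and the true error 5.7%. Attrition shrinks it further: at the 70% retention threshold of Section 2.4, groups of 7 become 4.9 on average, so at ICC 0.05 DE = 1.195, the SE ratio is 1.05 and the error about 6.1%.
- **Little turns on the p-value.** This stands. The trial is exploratory, states no alpha or power, and its Stop-Go rule uses retention and recruitment rates, which the outcome model does not touch.
- **The model may be completed in a statistical analysis plan.** This stands in part. The covariate list is open-ended, and the article neither excludes a group effect nor says that group membership goes unrecorded. But it does name a model and does assert, without qualification, that the variability data will be enough.
- **The next trial can bring its own design effect.** This stands against any claim of certain harm. A reader might infer that the definitive trial will be under-sized. The article says only that these statistics will inform the calculation, not that clustering will be ignored.
- **An ICC from 7 or 8 groups is too imprecise to use alone.** This stands, and it shapes the fix.
- **The calculation is for a simple two-arm contrast, not the adjusted model named.** This stands as a limit on precision: covariate adjustment could change the residual ICC. That controls are ungrouped is inferred from the waitlist design. When they receive TSR is not stated, so grouping of controls by the 1-month follow-up cannot be excluded.

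**Conclusion.** The point holds in a limited form. The model named in Section 2.4 has no term for the 7 or 8 therapy groups. If the ICC is positive, the SE of TSR versus waitlist at the postintervention assessment is too small. Over an assumed ICC of 0.01 to 0.10 and groups of 6 to 8, the correct SE is about 1.01 to 1.16 times the naive one, and the true error of a nominal 5% two-sided test is about 5% to 9%. This is modest and does not affect the feasibility decision.

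The firmer part is the planning claim. For a group-delivered intervention, SDs and Cohen's d without an ICC are not enough, and a trial sized on them with no design effect would risk being too small, needing about 15% to 30% more participants at ICC 0.05 to 0.10 with groups of seven.

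A reader might also infer that the variance handed on leaves out the group component. It does not: the raw SD includes at least 98.6% of the total variance in this range, and only the split is missing.

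**What to change.** - Record the TSR group number and facilitator-pair ID for each intervention participant.
- Fit the outcome comparison as a partially nested mixed model, with a random group effect in the TSR arm only, each control as its own unit, and Satterthwaite or Kenward-Roger degrees of freedom.
- Report the within-group ICC with its confidence interval, and say that 7 or 8 groups estimate it imprecisely.
- Reword the claim in Section 2.4: the variability data will inform the definitive sample size, which will also apply a design effect over a range of plausible ICCs rather than this trial's point estimate.
- State when waitlist participants receive TSR relative to the 1-month follow-up, so that it is clear whether controls are also grouped at that visit.

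The cost is small: the two identifiers in the database (group number and facilitator pair), some analysis wording, and slightly wider confidence intervals. Sample size and delivery of the intervention do not change.
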